### Randomization, allocation, and blinding

2.3

Participants will be randomly allocated to the IG or CG by a random numeric sequence prepared by the WINPEPI software (PEPI-for-Windows) [41] by an independent researcher who will be unaware of the numeric codes for the groups. This sequence will be generated into 16 blocks of four to eight people per block. The numeric sequence will be kept in sequentially numbered opaque envelopes according to the order generated by the software. This sequence will be kept confidential and stored in a location that blind assessors will not have access to. Participants will also be stratified according to the risk classification of ulcers (IWGDF grade 2 and 3 equally distributed). Thus, 30 participants will be stratified to the subgroup with ulcer risk 2, and 30 participants will be stratified to the subgroup with ulcer risk 3, totaling 60 participants.

After agreeing to participate in the study and signing an informed consent form, allocation to the groups will be made by another independent researcher who will not know the numeric code identifying the groups. All personal data will be kept confidential before, during, and after the study by coding the participants’ names. Only the nurse and the person receiving the treatment will know the meaning of the code. After allocation to the IG, digital orthoses will be made, and the participant will be able to pick them up 24 h later.

Due to the characteristics of the intervention, it will not be possible for the nurse responsible for making the orthoses to be blinded. Participants also cannot be masked regarding the intervention since the therapy modality to be applied (toe orthoses) is known to the general public, and the differences between intervention and non-intervention are completely evident. However, participants will not be aware of the study's hypothesis.

The data tabulation of all assessments and statistical analyses will be done by an independent researcher who is blinded to the intervention modality and numerical codes identifying the groups. Before each assessment, all participants will be instructed to not reveal which group they belong to (IG or CG), and this procedure will be reiterated at each new re-assessment.

### Trial arms

2.4

Both the IG and CG participants will be instructed to maintain self-care strategies at home, which include proper cleaning, drying the feet and between the toes, moisturizing the skin, and adequate nail trimming. In case of any participant from either group presenting any foot complications, such as a foot ulcer, the participant should immediately notify the researchers and receive guidance from the research team on how to proceed.

#### Control group

2.4.1

After randomization, CG participants will be attended by a nurse specializing in stomatherapy, dermatology, or clinical podiatry. Participants will receive foot care for the removal of calluses; referral (if necessary) to the Specialized Rehabilitation Center (Centro Especializado de Reabilitação; CER), a health facility linked to SUS, for the acquisition of insoles and/or custom-made shoes (when indicated); and guidance on the use of therapeutic footwear. After study completion, toe orthoses will be offered to CG participants according to their needs.

#### Intervention group

2.4.2

IG participants will receive the same instructions as the CG participants in addition to customized silicone orthoses for toe realignment according to their needs. When not using therapeutic footwear, common footwear will be accepted if it provides adequate fit to accommodate the orthoses comfortably in order to avoid possible trauma resulting from improperly sized footwear.

During the reassessments, IG participants will have their orthoses examined and repaired or replaced if necessary. The criteria for discontinuing orthosis use during the study will include moderate to severe pain or any other condition that exposes the participant to discomfort, trauma caused by the use of the orthoses, allergy to the orthosis material, difficulty adapting to the orthoses, and imbalance. Participants will be instructed to promptly report any type of adverse events or discomfort. The criterion for discontinuing the intervention will also include the participant's own withdrawal from the study. If the IG participant stops using the orthoses without any explanation, their participation in the study will be terminated and they will be considered a drop out.

A bunion (or hallux valgus) will be treated with a toe separator type of orthosis to realign the toe (Fig. 2A). For flexible claw toes, a subphalangeal orthosis will be provided for realignment (Fig. 2B). A flexible hammer toe will be treated with an omega-type orthosis that protects the back of the toe without covering the nail, anchoring the support points in the plantar region of the toes (Fig. 2C). Prominences of the metatarsal heads will be treated with a semi-rigid silicone metatarsal head protector orthotic, and in the areas where impact needs to be cushioned, extra soft silicone will be used (Fig. 2D).

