**Fig. 2 fig2:**
[figure not shown]
**–** Toe orthosis types: (A) toe separator-type orthosis, (B) subphalangeal orthosis for flexible claw toe, (C) omega-type orthosis, (D) orthosis for protection of the metatarsal heads.

To prevent adverse effects, IG participants will received orthosis guidance, such as cleaning the orthoses and interdigital spaces with soap and water, adequately drying the toes and interdigital region, using talcum powder to absorb moisture between the toes, always using the orthoses with appropriate footwear and with socks to promote sweat absorption and prevent orthosis displacement, using the orthoses during all day, except during bath and when sleeping, and monitoring the integrity of the orthoses and always reporting any changes in the feet or orthoses.

Throughout the study, possible adverse effects will be evaluated, such as skin irritation (redness, itching, contact dermatitis, or erosions), discomfort or pain sensation (bulky orthoses), muscle contractions, hyperkeratosis, increased foot sweating, or trauma from friction (caused by an orthosis that has folded or is poorly adjusted to the toes). Adherence to the intervention will be evaluated through scheduled reassessments every 3 months and weekly via WhatsApp messages.

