### Sample calculation and statistical analyses

2.7

The sample size calculation was performed using GPower v. 3.1 software [47] based on the primary outcome variable of the study: the presence of hyperkeratosis (pre-ulcerative lesions). For this outcome, the relative risk (RR) was calculated based on the incidence of hyperkeratosis after treatment with silicone digital orthoses in people with DPN from a previous study [35] using a contingency table. The sample size calculation used the following parameters: RR = 0.4913, test power = 0.80, α = 0.05, and a chi-squared test for contingency tables, resulting in a sample size of 54 participants. Assuming a 10 % loss to follow-up, 60 participants will be needed.

The inferential statistical analysis will be done by adopting an intention-to-treat approach. The imputation of missing values for the analyzed variables will be depend on the nature of the losses. After confirmation of normality (Kolmogorov–Smirnov test), homoscedasticity (Levene test), and imputation of means for missing data of variables with normal distribution, a two-way repeated measures ANOVA will be performed followed by Newman–Keuls post-hoc test to obtain group (CG and IG), time (baseline and 3 and 6 months), and group by time interaction effects. Significant differences will be considered with an alpha of 5 %. For the description of the intervention effect, the effect size (Cohen's d coefficient) and the difference between means with 95 % confidence intervals will be calculated.

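### Ending study participation for orthosis-group participants who stop the device without explanation conflicts with the declared intention-to-treat analysis

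*Protocol article*

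**What the plan says.** Section 2.4.2 (Intervention group) of the protocol article covers three situations.

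- **Explained stopping of the device.** "The criteria for discontinuing orthosis use during the study will include moderate to severe pain or any other condition that exposes the participant to discomfort"; the list continues with trauma from the orthosis, allergy to its material, difficulty adapting and imbalance. Device use ends. The text does not say that the participant leaves the study.
- **The participant's own withdrawal from the study.** This is listed as a separate criterion.
- **Unexplained stopping.** If a participant "stops using the orthoses without any explanation, their participation in the study will be terminated and they will be considered a drop out".

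The same section adds: "Adherence to the intervention will be evaluated through scheduled reassessments every 3 months and weekly via WhatsApp messages".

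Section 2.4.1 (Control group) contains no rule that ends anyone's participation. It mentions orthoses once: "After study completion, toe orthoses will be offered to CG participants according to their needs".

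Section 2.5 schedules the primary outcome, lesions and ulcers, at baseline, 3 months and 6 months in both groups. It does not say that terminated participants are still seen.

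Section 2.7 states: "The inferential statistical analysis will be done by adopting an intention-to-treat approach". Handling of missing values is to depend on the nature of the losses. The only method named is in this clause: "imputation of means for missing data of variables with normal distribution, a two-way repeated measures ANOVA will be performed". The sample size rests on "RR = 0.4913, test power = 0.80, α = 0.05, and a chi-squared test for contingency tables, resulting in a sample size of 54 participants", followed by "Assuming a 10 % loss to follow-up, 60 participants will be needed".

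**The concern.** Intention-to-treat compares the groups as randomised, and for that the outcome has to be sought from everyone, users and non-users alike. The rule in section 2.4.2 does the opposite for one kind of non-user. It stops outcome collection for people who have not asked to leave, and it can do so only in the orthosis group. With weekly contact about adherence, stopping may come to light, and participation end, before the 3-month or the 6-month assessment.

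What is at stake is the primary comparison. Outcomes missing in one arm because of behaviour after randomisation undo part of what randomisation provides. With about 30 participants per group, a handful of such losses matters, and data that were never collected cannot be recovered at analysis. The same visits also carry the safety, satisfaction and comfort questionnaires.

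**Working it through.** **1. The plan's own figure.** 54 / (1 − 0.10) = 60, as stated. The allowance is 60 − 54 = 6 participants, or about 3 per group at 1:1 allocation. The 54 itself would need a control-group risk that the article does not give; it is not used below.

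**2. The passages side by side.**

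| Situation | Device use | Follow-up |
|---|---|---|
| Orthosis group, explained stopping (2.4.2) | ends | termination not stated |
| Orthosis group, own withdrawal (2.4.2) | ends | ends, by the participant's choice |
| Orthosis group, unexplained stopping (2.4.2) | has ended | ended by the protocol |
| Control group (2.4.1) | not applicable | no termination rule |
| Analysis (2.7) | – | intention-to-treat |

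The third row cannot be squared with the last. The loss is imposed by the protocol, since own withdrawal is dealt with separately.

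**3. Whether the named imputation repairs it.** Mean imputation is stated for normally distributed variables. Lesion incidence is binary and the lesion grade (section 2.6.1) is ordinal with six levels; no method is named for either. If the mean of the remaining orthosis participants were filled in, the group's estimate would equal that of the remaining participants, so any selection would stay and the variance would be understated.

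**4. Illustration with a true effect.** Assumptions: relative risk 0.4913 in users (section 2.7); a fraction s of the orthosis group stops without explanation; stoppers carry the control-group risk from the start; and they are either left out or filled in with the mean of the remaining orthosis participants.

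Intention-to-treat relative risk = (1 − s) × 0.4913 + s. The control risk cancels.

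- s = 0.10: 0.4422 + 0.10 = 0.54
- s = 0.20: 0.3930 + 0.20 = 0.59
- s = 0.30: 0.3439 + 0.30 = 0.64

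Under these assumptions the reported value would be 0.49 in each case.

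**5. Illustration with no true effect.** Let stoppers have m times the risk of continuers. The whole orthosis group has the control risk, so the apparent relative risk among continuers is 1 / [(1 − s) + s × m].

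| s | m = 1.25 | m = 1.5 | m = 2.0 |
|---|---|---|---|
| 0.10 | 0.98 | 0.95 | 0.91 |
| 0.20 | 0.95 | 0.91 | 0.83 |
| 0.30 | 0.93 | 0.87 | 0.77 |

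The control risk cancels here too, provided it is low enough for m times the continuers' risk to stay below 1.

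**6. Direction.** If m is below 1, the sign turns. For example, s = 0.20 and m = 0.75 give 1 / (0.80 + 0.15) = 1.05, against the orthosis.

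**The case against.** The strongest reply is that the rule is narrow and its effect may be small. Four parts of it stand.

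- A reader might take the rule to cover everyone who stops the device, and conclude that the orthosis group is reduced to adherers. The text does not support this. Only unexplained stopping leads to termination; explained discontinuers and partial users are not said to leave. Participants are asked to report discomfort promptly and are contacted weekly, so many stoppers may have a reason on record.
- A reader might infer that drop-outs leave the analysis set. The article does not say so; it declares intention-to-treat with imputation. The 0.49 in the illustration holds only if stoppers are left out or filled in as described.
- A reader might infer a certain bias in favour of the orthosis. The listed reasons for stopping, such as pain or imbalance, belong to explained stopping. The documents show no link between unexplained stopping and lesion risk. Higher risk among these stoppers is plausible, but someone may also stop because the feet are doing well.
- The attrition allowance exists to absorb losses, and nothing shows that this rule would exceed it. The missing control-group counterpart is also partly structural, since that group has no orthosis to stop using.

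None of this removes the conflict. Intention-to-treat can be kept in name by imputing, but the rule still discards outcomes that a scheduled visit could have supplied, and in one arm only.

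**Conclusion.** The plan is wrong as written on this point, within limits. Section 2.4.2 creates avoidable, adherence-driven missing primary outcomes in the orthosis group alone, section 2.7 declares an analysis that needs those outcomes, and no other section repairs the conflict.

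The size depends on two unknowns: how many stop without explanation, and how their risk compares with that of continuers. At 10% stopping, which is 3 of 30 participants, the illustrations give 0.54 against 0.49 when the device works, and 0.98 to 0.91 instead of 1 when it does not. At 30% they give 0.64 against 0.49, and 0.93 to 0.77 instead of 1. These are ranges under stated assumptions and not forecasts. Bias towards the orthosis is the plausible direction but has not been shown.

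**What to change.** Delete the termination rule in section 2.4.2 and reconcile that section with section 2.7. State that a participant who stops using the orthosis, with or without explanation:

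- remains in the study and attends the scheduled 3- and 6-month assessments;
- is analysed in the group to which he or she was randomised, with orthosis use recorded.

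State that only the participant's own withdrawal from the study ends follow-up, and report any adherence-based analysis as secondary. The criteria for stopping the orthosis itself are unchanged.

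The cost is a short amendment and already scheduled visits for a few participants. Section 3.1 says that the trial is recruiting, so outcomes not yet lost can still be protected. The observed effect may be diluted, and power with it. With 30 per group, a two-sided 5% test, an assumed control risk of 0.70 and the assumptions of step 4, power with stoppers kept is 0.71, 0.61 or 0.50 at 10, 20 or 30% stopping, against 0.78, 0.76 or 0.72 with them left out. At an assumed control risk of 0.60 the figures are 0.57, 0.47 or 0.38 against 0.64, 0.61 or 0.58. The higher figures belong to a comparison restricted to continuers, which is not the one the protocol declares.

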**Fig. 2 fig2:**
[figure not shown]
**–** Toe orthosis types: (A) toe separator-type orthosis, (B) subphalangeal orthosis for flexible claw toe, (C) omega-type orthosis, (D) orthosis for protection of the metatarsal heads.

To prevent adverse effects, IG participants will received orthosis guidance, such as cleaning the orthoses and interdigital spaces with soap and water, adequately drying the toes and interdigital region, using talcum powder to absorb moisture between the toes, always using the orthoses with appropriate footwear and with socks to promote sweat absorption and prevent orthosis displacement, using the orthoses during all day, except during bath and when sleeping, and monitoring the integrity of the orthoses and always reporting any changes in the feet or orthoses.

Throughout the study, possible adverse effects will be evaluated, such as skin irritation (redness, itching, contact dermatitis, or erosions), discomfort or pain sensation (bulky orthoses), muscle contractions, hyperkeratosis, increased foot sweating, or trauma from friction (caused by an orthosis that has folded or is poorly adjusted to the toes). Adherence to the intervention will be evaluated through scheduled reassessments every 3 months and weekly via WhatsApp messages.

### Outcome assessments and timeline

2.5

Two researchers blinded to group allocation will perform the baseline and all follow-up assessments. IG participants will be assessed at baseline, after 7 days (via a telephone questionnaire about safety and comfort), at 3 months, and at 6 months. CG participants will be assessed at baseline and 3 and 6 months. Intervals of 3 and 6 months were established for the reassessments following the IWGDF guidelines, which recommend that individuals with DM classified as risk 2 need to be evaluated every 3–6 months and with risk 3 every 1–3 months. Table 1 presents the primary and secondary outcomes and the study period in which they will be evaluated according to the SPIRIT guidelines [40].

**Table 1 tbl1:** Primary and secondary outcomes of the study following the SPIRIT guidelines.

Outcomes		When participants will be assessed			
Primary	Measures	Baseline	7 days	3 m	6 m
Pre-ulcerative lesions and ulcers	Assessed according Colagiuri et al. (1995), which classifies hyperkeratosis into 6 grades.	**X**		**X**	**X**
**Secondary**	**Measures**				
Plantar pressure distribution during gait	Pressure peak, pressure-time integral, contact area by anatomical masking	**X**		**X**	**X**
Range of motion (ROM) of metatarsofalgeal joint	To assess ROM, a manual goniometer will be used to assess joint amplitude passively and actively	**X**		**X**	**X**
Toes alignment and flexibility	To measure toes alignment, toes will be photographed with markings on the metatarsophalangeal and interphalangeal joints.	**X**			**X**
Foot health and functionality	FHSQ-BR Domain scores	**X**		**X**	**X**
Quality of life	EQ-5D questionnaire	**X**		**X**	**X**
Satisfaction and safety	Satisfaction and Safety Questionnaires		**X**	**X**	**X**
Comfort	Analog numerical comfort scale		**X**	**X**	**X**

To ensure the eligibility criteria, all participants will undergo a baseline anamnesis, which will include questions about sociodemographic and anthropometric data, comorbidities, and the risk of developing ulcers. To verify the presence of DPN, peripheral arterial disease, and toe and forefoot deformities, we will follow the recommendations of the International Consensus on the Diabetic Foot [27]. The Semmes–Weinstein 10-g monofilament and a 128-Hz tuning fork will be used to check for loss of tactile and vibratory sensitivity, respectively. Peripheral arterial disease will be verified by palpation of the pedal and posterior tibial pulses in both limbs. The presence of at least one palpable pulse in each limb will rule out peripheral arterial disease. Toe and forefoot deformities, such as claw, hammer, and mallet toes; hallux valgus; reduced mobility; atrophy or displacement of the plantar fat pad; metatarsal head prominences; overlapping toes; and supraducts (Fig. 3), will be identified through observation. Study participants with an ulceration risk level of 2 (with toes deformities and DPN) or 3 according to the guidelines of the IWGDF [27] will be included. Those classified as having a risk of 0 or 1 will not be included in the study.

**Fig. 3 fig3:**
[figure not shown]
**-** Illustration of deformities at the forefoot region: (A) claw toe, (B) hammer toe, (C) mallet toe, (D) hallux valgus, (E) rigid or reduced hallux, (F) overlapping mobility toes, (G) fat pad atrophy, (H) prominence of the metatarsal heads, (I) supraduct toe.

### Primary and secondary outcomes

2.6

The incidence of ulcers and pre-ulcerative lesions will be considered the primary outcomes. The plantar pressure distribution during walking, metatarsophalangeal joint range of motion (ROM), toe alignment, foot function, overall foot health, quality of life, satisfaction, safety, and comfort will be secondary outcomes.

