**Methods:**

In this superiority randomized controlled parallel trial with single-blind assessment, 60 participants will be allocated to the control group (CG) or the intervention group (IG). The CG will receive specialized nurse-administered foot care, including callus removal, nail care guidance, and self-care education. The IG will receive the same care plus a customized silicone orthosis for toe realignment for 6 months. Assessments will occur at baseline and 3 and 6 months for the primary outcomes (pre-ulcerative lesions and ulcer incidence) and secondary outcomes (pressure distribution, foot function and health, quality of life, safety, and comfort). Two-way ANOVAs (p < .05) will assess group, time, and group by time effects following an intention-to-treat approach.

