### Participants and recruitment

2.2

Participants will be recruited from private clinics linked to the Brazilian Unified Health System (Sistema Unico de Saúde; SUS) that are specialized in preventing and treating the diabetic foot as well as from clinics specialized in treating wounds. Participants will undergo an initial assessment for screening and confirmation of eligibility criteria. Inclusion criteria will be people of both sexes ages 18–75 years who are diagnosed with type 1 or 2 DM with DPN as confirmed by loss of sensitivity measured by Semmes–Weinstein 10-g monofilament, a 128-Hz tuning fork, and the fuzzy score of DPN severity (www.usp.br/labimph/fuzzy); have one or more forefoot flexible deformities (claw, hammer, mallet, or overlapping toes; bunion; prominences of the metatarsal heads; or decrease/displacement of adipose cushion); and are able to independently walk with or without an assistive device. The non-inclusion criteria will be other diagnosed neurological diseases, major vascular complications, receiving any physiotherapy interventions for the lower limbs during the entire intervention period, not performing foot-ankle exercises, having a callus grade 5 or 6 at baseline, major amputations in both limbs (above the ankle), minor amputations in the foot that will receive the orthosis (Chopart, Lisfranc, transmetatarsal), and the presence of dementia or inability to provide consistent information.

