#### Pre-ulcerative lesions and ulcers

2.6.1

The assessment of pre-ulcerative lesions (hyperkeratosis) and ulcers will be performed according to the study by Colagiuri et al. [42], in which pre-ulcerative lesions and ulcers were evaluated using six grades, as follows (Fig. 4):1.Grade 1: minimal thickening of the keratin layer2.Grade 2: moderate thickening of the keratin layer3.Grade 3: marked thickening of the keratin layer4.Grade 4: callus with subcutaneous bleeding5.Grade 5: callus with ulcer6.Grade 6: callus with infected ulcer

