**Fig. 4 fig4:**
[figure not shown]
Grades 1 to 6 of severity of pre-ulcerative lesions and ulcers.

Grades 1 to 4 refer to pre-ulcerative lesions, while Grades 5 and 6 are already established ulcers. If the participant is classified as Grade 5 or 6 at baseline assessment, they will not be included in the study but may be included later after the ulcer has healed.

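### The primary outcome is stated inconsistently: two primaries called incidence, but a trial sized on the presence of one, in people who may already have it

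*Protocol article*

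**What the plan says.** All references are to the protocol article.

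- **Primary outcomes.** Section 2.6: "The incidence of ulcers and pre-ulcerative lesions will be considered the primary outcomes". The abstract also uses the plural: "primary outcomes (pre-ulcerative lesions and ulcer incidence".
- **Sizing.** Section 2.7 bases the sample size on "the primary outcome variable of the study: the presence of hyperkeratosis (pre-ulcerative lesions". It uses RR = 0.4913, 80% power, alpha 0.05 and a chi-squared test, which gives 54 participants, or 60 after 10% loss. Ulcers do not enter the calculation. The analysis paragraph states one 5% alpha.
- **Scale.** Section 2.6.1 lists six grades, the lowest being "Grade 1: minimal thickening of the keratin layer". Then: "Grades 1 to 4 refer to pre-ulcerative lesions, while Grades 5 and 6 are already established ulcers". No code for a foot without a lesion is listed.
- **Entry.** Section 2.2 bars people "having a callus grade 5 or 6 at baseline". Grades 1 to 4 are not barred.
- **Care in both arms.** Section 2.4.1: "Participants will receive foot care for the removal of calluses". Sections 2.1 and 2.4.2 give the intervention group the same care plus the orthosis.
- **Visits.** Table 1 has a single primary row, pre-ulcerative lesions and ulcers, assessed at baseline, 3 months and 6 months. No visit is named as primary.

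**The concern.** Incidence counts new events among people, or sites, that were free of the event at the start. Presence counts everyone who has the event at a visit, whatever their starting state. The two agree only if everyone starts clear. Here people may enter with the event, have it removed, and have it return. The introduction itself says that hyperkeratosis re-forms when its mechanical cause is not dealt with, so such cases should be common. Whether a returning callus counts decides both the denominator and the event rate.

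The number of primary outcomes is also unclear. Sections 2.6 and the abstract point to two; section 2.7 points to one. If ulcers are a separate primary, the trial carries a test that it was not sized for, and nothing says whether one significant result is enough or both are needed. At stake are an undeclared rise in the false-positive rate, an ulcer result that says little either way, and a definition that could be settled after data are seen.

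**Working it through.** **1. The plan's own figure.** 54 / 0.90 = 60, so the loss allowance reproduces. The 54 itself depends on a control risk that the article does not give. With RR 0.4913, 1:1 allocation, a two-sided uncorrected test and 80% power, the total is 56 at a control risk of 0.72 and 52 at 0.75. It also results exactly if 0.4913 is entered as the chi-squared effect size w with 5 degrees of freedom: 12.8276 / 0.4913² = 53.1, rounded up to 54. The article does not say which was done. Either way, ulcers are not in it. Below, 27 per arm is 54 / 2.

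**2. Incidence against presence.** Assume a control risk of 0.70 among people lesion-free at entry. The intervention risk is then 0.70 × 0.4913 = 0.344, and the difference d = 0.356. Power = Φ[(d − 1.96·SE0) / SE1], where SE0 uses the pooled risk and SE1 the separate risks.

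- All lesion-free (27 per arm): SE0 = 0.136, SE1 = 0.127, so Φ[(0.356 − 0.266) / 0.127] = Φ(0.71) = 76%.
- 80% lesion-free (21.6 per arm): 66%.
- 50% lesion-free (13.5 per arm): SE0 = 0.192, SE1 = 0.180, so Φ[(0.356 − 0.377) / 0.180] = Φ(−0.12) = 45%.

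For presence, all 54 count. If re-formation after debridement responds to the orthosis like new formation, power stays at 76%. At the other extreme, half enter with a lesion and every one of those has a lesion again at the visit. The risks become 0.5 + 0.5 × 0.70 = 0.85 and 0.5 + 0.5 × 0.344 = 0.672, the RR is 0.79, and power is 33%. The share lesion-free at entry is not in the article; these are illustrations.

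**3. Error rate with two primaries.** If either alone may win and each test is at 5%, familywise error is at most 0.05 + 0.05 = 10%, and 1 − 0.95² = 9.75% if the tests are independent. With few ulcers the ulcer test may not spend its 5%. Exact enumeration of the ulcer test's true size at 27 per arm, combined as 1 − 0.95 × (1 − size):

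| Assumed ulcer risk | Size, chi-squared | Familywise | Size, Fisher | Familywise |
|---|---|---|---|---|
| 5% | 2.3% | 7.2% | 0.1% | 5.1% |
| 10% | 5.2% | 9.9% | 0.7% | 5.7% |
| 20% | 5.7% | 10.4% | 1.9% | 6.8% |
| 30% | 5.5% | 10.2% | 2.5% | 7.4% |

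The values just over 10% arise because the uncorrected chi-squared test slightly exceeds 5% at this sample size. If both outcomes had to be significant, there would be no inflation, but ulcers would limit the power.

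**4. Power for ulcers.** Exact enumeration, 27 per arm, with RR 0.4913 carried over to ulcers (an assumption):

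| Assumed control risk | Expected ulcers, control v intervention | Chi-squared | Fisher | Total N for 80% power (normal approximation) |
|---|---|---|---|---|
| 5% | 1.4 v 0.7 | 2% | 0.1% | 1740 |
| 10% | 2.7 v 1.3 | 9% | 1.4% | 836 |
| 20% | 5.4 v 2.7 | 19% | 8% | 384 |
| 30% | 8.1 v 4.0 | 29% | 17% | 232 |

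**The case against.** The strongest reply has four parts.

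**The scale.** Because Grade 1 already means thickening and Grades 1 to 4 all count as lesions, a reader might infer that every graded foot is an event, that the event rate is 100% in both arms and that the arms cannot differ. The documents do not support that. The grades rate the severity of a lesion that is present. Sizing on presence with a contingency table implies that absence is possible, and nowhere must every foot receive a grade. This reply stands. What remains is that absence has no explicit code.

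**Counting incidence.** Both arms are debrided after randomization, so re-formation by 3 or 6 months is a coherent event. The detailed rule may sit in a full protocol or analysis plan that is not shown. This stands in part: the endpoint is not uncountable, and a missing operational rule alone would be no finding. But the clash between incidence and presence, and the eligibility of Grades 1 to 4, are printed in the article.

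**One primary.** Table 1 has one row on one scale, and section 2.7 speaks of a single primary variable, so one graded or composite outcome is a possible reading. Under it the multiplicity concern falls away. But section 2.6 and the abstract use the plural, and nothing reconciles them.

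**The error rate.** No text says that either result alone would count as success, and the two outcomes come from one scale, so independence is implausible. This stands: about 10% is a ceiling under one reading, not an expected value.

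**Conclusion.** The inconsistency is real and should be resolved, but it does not make the trial unanalysable. The article names two primary outcomes as incidence in one place and sizes one outcome as presence in another, while admitting people who already have that outcome.

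The choice matters. With an assumed control risk of 0.70, power for incident lesions runs from 76% to 45% as the lesion-free share falls from all to half. The either-wins reading allows a familywise error above 5%, at most about 10%, and close to 5% if ulcers are few and Fisher's test is used. As a separate primary, ulcers have about 2% to 29% power (Fisher 0.1% to 17%).

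Control risks, ulcer risks, the lesion-free share and the use of the hyperkeratosis RR for ulcers are all assumptions. The finding that ulcers were not sized for needs none of them.

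**What to change.** Amend sections 2.6, 2.6.1 and 2.7, the abstract and the registry entry so that they state the same single primary outcome:

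1. Presence of a forefoot pre-ulcerative lesion or worse, per participant, at one named visit, with the grade cut-off fixed now. This matches the sized variable.
2. An explicit code for no lesion on the form.
3. Grading before any debridement at that visit.
4. Adjustment for the baseline grade, which Table 1 already collects.
5. Ulcers (Grades 5 and 6) as a secondary outcome, reported with confidence intervals.

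A prespecified composite or ordinal primary would also settle the matter; the essential point is that one definition is fixed before outcome data are seen by group. Section 3.1 says recruitment is under way, so this is needed soon.

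The cost is an amendment, a registry update and one extra code. The downside is that ulcer prevention is no longer a co-primary claim. Keeping both primaries with alpha split to 0.025 would cost more: at RR 0.4913 the total before dropout rises from 60 to 74 at an assumed control risk of 0.70, or from 82 to 100 at 0.60, and ulcers would still be underpowered.
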